## Abstract

**Background:**

Social care is vital to quality of life for people with young onset dementia and their families. Yet care is hugely variable, frequently lacking and poorly coordinated. We aim to establish current practice in English social care for people with young onset dementia and co-produce evidence-based recommendations and resources for improvement.

**Methods and analysis:**

In Work-Package 1, we will gather qualitative data from 25 people with young onset dementia and/or main supporters residing in England. We will ask them about their experiences of social care (broadly defined, including independent and voluntary sector provision) and suggestions for improvement. In Work-Package 2, we will conduct a short on-line survey with a wide range of staff with a role in adult social care in England. We will find out about current awareness, knowledge and practice and suggestions for improvements. Quantitative and qualitative analysis will provide a picture of current practice. In Work-Package 3, we will use convergence analysis to synthesise the findings from Work-Packages 1 and 2 and present the findings to a stakeholder workshop, to identify feasible priorities for improvement. We will establish what is already known about good practice relating to these key priorities using a scoping review and interviews with professionals. This knowledge will then feed into the co-production of resources and recommendations with key stakeholders to improve social care for people with young onset dementia and their families.

**Discussion:**

This study seeks to address a gap in our understanding of social care provision for people with young onset dementia and develop recommendations and practical resources for improvements. The findings will help people with young onset dementia and supporters to receive higher quality social care.

**Trial registration:**

**Study registration number:**
ISRCTN10653250.

## Introduction

It is estimated that 55 million people are currently living with dementia worldwide, a number estimated to increase to 139 million by 2050 [1]. There are many different types of dementia. Although young onset dementia (dementia with an onset under 65 years of age) is relatively rare, its prevalence in the UK at 70,800 [2] is higher than other well-known conditions, e.g. over 8 times as many people have young onset dementia than have motor neuron disease [3]. The condition has great impact on those diagnosed and costs families the equivalent of £10,000 in family care per 3 months [4]. There is also a wider cost to society as both the person diagnosed and/or their main supporter may be unable to work [5]. There are also long-term consequences for the well-being, education and mental health of children/young people in the family [6, 7]. Formal services currently fund little care or support for people with young onset dementia, unless the person is admitted to residential care [4].

Social care has an important role in supporting individuals. The purpose of social care planning is to enable people to remain independent, have control over their life, do things they enjoy, know what type of care may help and understand their condition and care needs [8, 9]. Social care is vital to the quality of life of people with young onset dementia and their families [10, 11] but their social care needs are seldom well addressed [4, 6, 12]. Research in the Angela Project found that almost a third of people living with young onset dementia had no regular appointments with any social or health care professional and fewer than 1 in 3 had a care plan [6]. Lack of social care has far-reaching consequences, exposing people with young onset dementia and their families to risks, including strained relationships, financial hardship, mental distress and ill-being. Unmet social care needs are significantly associated with distress and psychiatric symptoms [13]. They may precipitate crises for the person with young onset dementia and their families [7]. Services may then have to step in to address issues that could have been averted by earlier social care provision. There is a great need to improve social care for people with young onset dementia to address the inequalities experienced by this population.

There is little published research and no published reviews specifically addressing young onset dementia social care. A 2016 review on young onset dementia [12] found only 10 sources focused on service experiences, concluding that there was: ‘lack of a clear diagnostic pathway, poor provision of information, lack of appropriate referrals to support services, and a high volume of informal care provided’ (p.5). A 2018 systematic review [10] of service provision for people with young onset dementia located six UK-based studies on social care needs and service provision. The authors concluded these initiatives enabled people with young onset dementia to continue living at home for longer but also that: ‘The evidence on the experience of living with young onset dementia is not matched by research and the innovation needed to mitigate the impact of young onset dementia’ (p.933). A 2022 meta-synthesis [8] identified 11 publications on views of specific supportive services and found there was great overlap in preferences of those with young onset dementia and their carers. The authors identified the need for further studies that include both people with young onset dementia and their carers and focus specifically on services. Against this backdrop of limited research, the Angela project [14], identified eight key needs of people with young onset dementia and family members, highlighting a strong social care component [15, 16]. The project confirmed that care was hugely variable, frequently lacking and poorly coordinated [4]. In particular, the person with young onset dementia was often discharged from secondary to primary health care, with little focus on social care [4]. Due to the predominantly healthcare focus of the Angela project, findings on social care were patchy and ‘fragmented’. Additionally, as the Angela project focused on positive experiences of diagnostic and post-diagnostic services, it did not identify unmet social care needs or shortcomings in services. Given the lack of research in this area, it is essential to establish gaps in social care practice and areas for improvement to inform the development of recommendations and resources to improve social care for people with young onset dementia.

Research [4, 10–12, 15, 17] has established the high level and breadth of social care needs in young onset dementia, the lack of social care for young onset dementia and the deleterious consequences of living with unmet social care needs for the person [13], main supporter [4, 17] and children/young people within the family [6, 7]. When developing this study our consultation work with a range of stakeholders indicated that no-one seems to have a clear picture of current social care for young onset dementia. In this project, we aim to address this gap and co-produce evidence-based recommendations.

## Objectives

The DYNAMIC study aims to:

Gain in-depth understanding of the social care needs, experiences and preferences of those living with young onset dementia and their supporters.Establish levels of awareness, knowledge and practice among professionals regarding social care needs, care planning, and provision for people with young onset dementia.Co-produce recommendations and resources to improve social care for people with young onset dementia and their supporters.

## Materials and methods

In this study we aim to establish current practice in English social care for people with young onset dementia and co-produce evidence-based recommendations and resources to improve social care. This study involves two stages: The first stage (to establish current practice) incorporates Work-packages 1 and 2 and Work-package 3 (to co-produce evidence-based recommendations and resources) will comprise the second stage.

### Work-package 1

In this Work-package we will employ qualitative methods to better understand experiences of social care and areas for improvement from the perspectives of people living with young onset dementia and their main supporters. Recruitment for this Work-package commenced on 3/11/2023.

We will recruit 25 ‘cases’, with each case constituting an individual with young onset dementia and/or a main supporter (typically a family member or friend), from England. People with young onset dementia who do not have a main supporter will still be eligible to participate in the study. The inclusion and exclusion criteria are provided in Box 1.

Box 1INCLUSION CRITERIAFor people with dementia:Diagnosed with young onset dementia (defined as when the first symptoms of dementia occur before the age of 65 years)Living alone or living with othersFor main supporters:Relatives, friends or neighbours self-identified as involved in supporting a person with young onset dementia.May be living within or outside the home environment of the person with dementia.Staff will be:Staff with a role in or awareness of adult/older adult social care planning, provision, management or commissioningEXCLUSION CRITERIAPeople with dementia will be excluded if they are any of the following:Diagnosed with dementia caused by HIV, traumatic brain injury, Down’s syndrome, Huntington’s chorea or alcohol-related dementia.Lack capacity to consent.Unable to communicate.Residing outside of England.Main supporters will be excluded if they are any of the following:Not caring for someone with young onset dementiaCaring for the person in a professional capacity e.g. paid carers.Residing outside of EnglandStaff will be excluded if they:Do not have a role in or awareness of adult/older adult social care planning, provision, management or commissioning.Work outside of England.

We will raise awareness of the study and recruit potential participants through a variety of media, including face-to-face meetings, with the help of national and local charitable and community-based organisations. Purposive sampling will ensure variation in characteristics that may influence experiences of social care e.g. gender, ethnicity and type of dementia. We will ensure inclusion and representation through consultation with patient and public involvement (PPI) members of the project team about the recruitment strategies. People who express an interest in taking part will be screened to ensure they meet the inclusion criteria.

We will offer a range of ways for people to express interest in taking part including in person (when the researcher visits community and peer support groups), online (by clicking a link or using a QR code), or by directly phoning or emailing the researcher. The researcher will contact those who express an interest to answer any questions about the study and check the individual meets the inclusion criteria. If the person meets these criteria the researcher will send them the information sheet (through email or post) and follow this up with further phone/email contact. Those who are ineligible or do not wish to participate will have their details destroyed. If the person has capacity to give informed consent and decides to take part the researcher will arrange a date and time for the research interview. The interview will take place in person, online or over the phone depending on the preference of the individual. Those with young onset dementia will be given a choice of having someone they trust present to support them. If both a person with young onset dementia and a supporter take part, they will be given a choice to be interviewed jointly or individually. Participants will be contacted with a reminder about the interview through their preferred contact method 1–2 days before the date of the meeting. In-person interviews will be conducted at the home of the interviewee or a mutually agreed suitable location, e.g. University premises.

On the day of the interview the researcher will re-confirm the participant’s capacity to consent and obtain consent either orally or in writing before the interview commences. Interviews will take the form of an extended conversation [18] guided by a semi-structured topic guide, allowing participants to focus on issues of most importance to them and enabling the researcher to probe for greater depth. Potential topics include experiences of social care; social care needs (met and unmet); contextual factors and nuances of the person’s unique situation, and suggested improvements or changes to social care provision. The interviews will last approximately 30–45 minutes but could be conducted over two occasions at participants’ requests. Interviews will be digitally recorded and transcribed. Participants will be given a voucher as a token of appreciation for their time.

Data will be managed using the Framework approach [19] and analysed inductively using reflexive thematic analysis [20]. We will take an ‘experiential’ approach, focusing on the meanings and experiences articulated by participants, underpinned by hermeneutics of empathy [20]. From this approach, themes are ‘conceptually founded patterns’ [21] reflexively developed by the research team but grounded in the expressed experiences of participants. After initial familiarisation and summarising, development and refinement of themes will be undertaken using a series of case by theme matrices (frameworks) to enable us to visualise relationships between cases, topics and themes. Involvement of the project team (including PPI members) at key points will bring in multiple perspectives, reducing the influence of any one researcher and ensuring rigour and accountability throughout [22].

### Work-package 2

In this work-package we will employ a quantitative methodology to establish awareness, knowledge and practice among staff regarding social care needs, care planning and provision for people with young onset dementia. This will involve a short on-line survey distributed across England.

Participants will be staff with a role in or awareness of adult social care planning, provision, management or commissioning. Staff could be employed by Local Authorities, the third sector, the healthcare sector, the private sector or integrated care boards. They do not have to have seen people with young onset dementia but need to have a remit that could include people with young onset dementia. The inclusion and exclusion criteria are listed in Box 1. To ensure recruitment across the whole range of social care professionals, we aim to establish the size and nature of the key population/ subpopulations (e.g., social workers, home carers, social prescribers) and check the distribution of respondents two and four months into recruitment. This will allow us to target later recruitment drives to increase representation from under-represented groups. Socio-demographic questions will enable us to check diversity of recruitment and this will allow focused recruitment campaigns.

The survey will be publicised through social media, key contacts of the research team and existing networks such as the Association of Directors of Adult Social Services. The publicity leaflet will include a link to the online survey. Contact details of the researcher will be provided so that those interested in taking part can find out more information about the study. The information sheet will be accessible through a link in the online survey or posted to those participants who request it. The survey will be available on paper for participants who do not have access to the internet or prefer to complete a paper version.

The survey will be kept concise and primarily consist of closed-ended questions, with some open-ended questions to enable participants to elaborate on their responses. Survey items will be informed by previous research and consultation with PPI members of the project team. Questions will address frequency of contact with people with young onset dementia; practice in the provision of social care in young onset dementia; and perceived areas for improvement in social care. We will also collect participants’ socio-demographic information and geographical location (e.g. rurality and ethnicity). To ensure the appropriateness of the length, wording, and content we will pilot the survey and will also use cognitive interviewing, where the person ‘thinks aloud’, explaining their thoughts as they answer each question [23], with at least two individuals.

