### Data analysis

All data will be imported into SPSS for analysis. We will produce descriptive data; for example, about the frequency of contact with people with young onset dementia. Some open-ended data will be imported into NVivo (qualitative data management software) or Excel for analysis. Content analysis [24] will be used to analyse responses to open-ended questions, and identify common themes, or categories, in participants’ responses; for example, in relation to improvements in social care. Emergent themes will be discussed with the wider research team, including PPI members, to ensure rigour in data analysis and relevance of the findings [22].

### Work-package 3

This Work-package will have several stages. The first stage comprises a synthesis of Work-package 1 and Work-package 2 findings to identify potential areas for improvement in social care provision. Themes from work-packages 1 and 2 will be compared to identify areas of convergence (similarities) and divergence (differences) [25]; e.g., if few Work-package 1 participants report receiving a social care assessment, this can be compared with Work-package 2 findings on staff reports of conducting social care assessments for people with young onset dementia. A consistent finding (e.g. few received and few delivered) could indicate a gap in provision, whereas an inconsistent finding (e.g. few received but many delivered) could indicate a mismatch of perceptions, implying a need for clearer communications. Suggestions for service change and improvement will be directly compared. These could include aspects such as improving social workers’ awareness of the impact of young onset dementia or development of more meaningful personalised care plans. The synthesised findings of Work packages 1 and 2 will be summarised for the next stage.

The second stage will involve identifying impactful feasible priorities for improvement in social care provision. Priorities will be established through an on-line consensus workshop. A purposive sample of up to 20 diverse stakeholders will be recruited through our existing contacts with organisations and individuals and the suggestions of Steering Group members. People who took part in Work-packages 1 and 2 will also be approached to take part. Stakeholders will include those with young onset dementia and main supporters, local authority and third sector staff. PPI members of the research team and the PPI lead will advise on ways to ensure meaningful involvement.

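### The Work-package 2 survey is self-selected, and its stated recruitment checks leave out contact with young onset dementia, so overall levels for Objective 2 may be overstated

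*Protocol article*

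**What the plan says.** The second objective (Protocol article, Objectives) is to "Establish levels of awareness, knowledge and practice among professionals regarding social care needs, care planning, and provision for people with young onset dementia". Work-package 2 repeats it as a quantitative aim: "we will employ a quantitative methodology to establish awareness, knowledge and practice among staff regarding social care needs". The intended population is wide. Of staff, the section says (final word omitted) "They do not have to have seen people with young onset dementia but need to have a remit that could include people with young onset".

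Recruitment is open. "The survey will be publicised through social media, key contacts of the research team and existing networks", and "The publicity leaflet will include a link to the online survey". The article describes no sampling frame or random selection.

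Two checks on who responds are described. The team will establish the size and nature of the role subpopulations and compare the distribution of respondents two and four months into recruitment, so that later drives can reach groups that are short. In addition, "Socio-demographic questions will enable us to check diversity of recruitment and this will allow focused recruitment campaigns".

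Frequency of contact with people with young onset dementia is listed as survey content. The Data analysis section gives it as an example of an output: "We will produce descriptive data; for example, about the frequency of contact with people with young onset dementia". It is not named among the recruitment checks.

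The Work-package 3 section then sets staff reports against the accounts from Work-package 1. Low receipt with low delivery could point to a gap in provision. Low receipt with high delivery could point to differing perceptions and a need for better communication.

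**The concern.** A level among staff can be read from a voluntary survey only if the people who answer resemble the people who do not, on whatever drives the answers. Here the topic itself is likely to drive response. Staff who know or work with young onset dementia have more reason to open the link and finish the survey, and are more likely to be reached through the research team's contacts. The same staff probably have higher awareness and knowledge. For delivery items the tie is almost definitional, since someone who has never met a person with the condition cannot have assessed one.

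The plan recognises that representation needs watching and schedules two checks, but the checks leave out this characteristic. A sample could match the workforce on role and socio-demographics and still over-represent staff with contact.

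Two things are at stake: the levels that Objective 2 asks for, and how much weight the Work-package 3 comparison can put on what staff report delivering. An overstated delivery figure leans towards the differing-perceptions reading and away from the gap-in-provision reading.

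**Working it through.** The article gives no sample size, response rate, precision or expected level for the survey, so there is no stated figure to reproduce. The calculation below is an illustration, and every input is an assumption.

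**Definitions**
- q: share of eligible staff with contact.
- r: response probability of staff with contact divided by that of staff without.
- p1, p0: proportion with the outcome (for example, adequate knowledge) among staff with and without contact.
- s: share of respondents with contact, s = qr / (qr + 1 − q).

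**Formulas**
- True level = q·p1 + (1 − q)·p0.
- Level among respondents = s·p1 + (1 − s)·p0.
- Bias = (s − q)(p1 − p0). It is zero when r = 1 (then s = q) or when p1 = p0.

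**Central illustration: q = 20%, p1 = 60%, p0 = 20%**
- True level: 0.2 × 0.6 + 0.8 × 0.2 = 28%.
- r = 2: s = 0.4 / 1.2 = 33.3%, level 33.3%, bias +5.3 points.
- r = 3: s = 0.6 / 1.4 = 42.9%, level 37.1%, bias +9.1 points.
- r = 4: s = 0.8 / 1.6 = 50%, level 40%, bias +12 points.
- r = 5: s = 1.0 / 1.8 = 55.6%, level 42.2%, bias +14.2 points.

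**Range.** With p0 = 20%, q from 10% to 30%, p1 from 30% to 60% and r from 2 to 5, the bias runs from +0.8 points (q = 10%, p1 = 30%, r = 2) to +15.3 points (q = 30%, p1 = 60%, r = 5).

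**Does balancing roles remove it?** Take two roles, each exactly half of the population and half of the sample.
- Role A: q = 30%, p1 = 60%, p0 = 30%. True level 0.3 × 0.6 + 0.7 × 0.3 = 39%.
- Role B: q = 10%, p1 = 40%, p0 = 10%. True level 0.1 × 0.4 + 0.9 × 0.1 = 13%.
- Overall true level: (39% + 13%) / 2 = 26%.
- r = 2: A 43.8%, B 15.5%, overall 29.7%.
- r = 3: A 46.9%, B 17.5%, overall 32.2%.
- r = 5: A 50.5%, B 20.7%, overall 35.6%.

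The role mix is perfect, yet the overall level is 3.7 to 9.6 points too high. Weighting by role would do no better, because the selection acts within each role.

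**A delivery item.** Let p0 = 0, q = 20% and p1 = 60%.
- Over all eligible staff, the true level is 0.2 × 0.6 = 12%.
- Over all respondents, it reads 0.333 × 0.6 = 20% at r = 2 and 0.5 × 0.6 = 30% at r = 4.
- Among staff with contact, it reads 60% whatever r is, provided response within that group does not depend on delivery.

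For delivery items, the choice of denominator therefore decides whether this bias enters at all.

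**The case against.** The strongest points on the other side are these.

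- **Enrichment is inferred, not stated.** The one network the article names is a general adult social care body, and the leaflet and opening page are not shown. This stands. The claim can only be that staff with contact are likely to be over-represented.
- **The plan is partly protected.** Staff without contact are eligible, later drives target groups that are short, and contact frequency is collected and reported. This stands in part. Eligibility lets low-contact staff answer without making them equally likely to, and reporting contact frequency helps readers only if the other results are set against it.
- **Stratified tables may already be intended.** A reader might infer that results will be reported only as one combined figure, or that the role sizes serve recruitment alone. The article says neither, and a condensed article may leave table layouts to the full protocol or analysis plan. No criticism is made on that ground. The recruitment checks are different, because the article itself states what they cover.
- **Delivery items have a natural denominator.** Among staff with contact, over-representing that group does not by itself bias the figure. This stands and shapes the fix. The concern applies to awareness, knowledge and delivery figures taken over all respondents.
- **There is no benchmark for contact.** The documents give none, so an interim check cannot prove over-representation. This stands. The check would still show whether low-contact staff are being reached at all.

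**Conclusion.** The point holds as a gap in the stated recruitment safeguards. The survey seeks levels in a population that includes staff without contact, recruits by self-selection, and does not check the collected variable most closely tied to both response and outcome. Overall levels are likely to err upwards. The size is unknown: about +1 to +15 points under the assumed inputs, and zero if response or outcome does not differ by contact.

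A reader might go further and infer that the survey will turn a real gap in provision into an apparent difference of perceptions. The documents do not support that. The Work-package 3 section sets no numerical threshold, compares themes and says only what each pattern could indicate. Priorities are then settled at a workshop of up to 20 stakeholders. In the central illustration the level moves from 28% to between 33% and 42%, which is still a minority, so low delivery does not become high delivery. The bias tilts the evidence but does not by itself decide the reading.

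**What to change.** 1. **Recruitment.** Add frequency of contact and recruitment route to the two- and four-month checks. Aim later drives at low-contact staff and at networks beyond the team's own contacts. Treat the check as showing the spread of contact, not as proof of over-representation.
2. **Reporting.** Present awareness and knowledge by contact level, and by role. Report delivery items among staff with contact and state that denominator. Describe any overall figure as the level among respondents. Do not rely on role weighting to remove the bias.
3. **Synthesis.** Carry the same caution into the Work-package 3 convergence step before low receipt alongside high delivery is read as differing perceptions.

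The cost is small. Contact is already asked and the checks are already scheduled. Recruitment route may need one short extra item. The price is smaller cells and a less sweeping headline figure. Step 1 helps only while the survey is open; steps 2 and 3 remain possible afterwards. Stratifying by contact will not remove selection by interest among staff with the same level of contact, which is a further reason for the respondents-only wording.
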